#### Treatment planning

Eligible patients will be asked to provide informed consent to participate in the study. Next, the interventional radiologist and nuclear medicine physician will make an individualized treatment plan (including identification of the target vessels for selective infusion, identification of extrahepatic branches, and determining the need for coil embolization), based on the anatomy of the hepatic arterial vasculature visualized on pretreatment CT images. In all procedures, two selective injection positions (in the left and right hepatic artery) will be used to treat the whole liver on the same day. In patients with a variant hepatic arterial configuration, intrahepatic arterial branches (for example, the segment 4 artery) may be coil embolized to induce redistribution of blood flow through intrahepatic collaterals, and enable the use of two selective injection positions.

The total amount of ^166^Ho activity (A_Ho166_) required to deliver a whole liver absorbed dose of 60 Gy – the maximum tolerable radiation dose previously determined in a phase I dose-escalation study – is calculated using the formula:$$ {A}_{Ho166}(MBq)=\frac{60\;(Gy)}{15.87\;x\;{10}^{-3}\;\left(J/ MBq\right)}\;x\; Liver\; weight\;(Kg) $$Liver weight (in Kg) is determined by multiplying the volume of the liver (measurement based on CT) with the density of liver tissue (1.06 g/cm^3^). The scout procedure always consist of 250 MBq in 60 mg of microspheres (density 1.4 g/cm^3^), this activity is subtracted from the activity given in the treatment procedure. The treatment activity for each perfusion territory is fractionated based on its liver volume. If coil embolization of an intrahepatic branch is planned, the volume of its perfusion territory is included in the side that is anticipated to take over the blood supply.

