### Outcome assessment

In every target vessels’ perfusion territory, the absorbed dose on ^166^Ho-SPECT reconstructions will be determined for the metastases and the healthy liver tissue [4]. Consequently, a posttreatment T/N activity ratio will be calculated for each perfusion territory by dividing the number of counts in tumorous and healthy liver tissue.

The predictive value of the scout dose will be assessed by comparison of the distribution of the scout dose with the treatment dose. The analysis will be based on tumor and healthy liver absorbed doses on SPECT/CT analysis.

Infusion efficiency is defined as the percentage of the prepared treatment activity that is infused. The ^166^Ho activity that is not infused will be determined by measuring the administration system (vial, lines, and catheters) with a dose calibrator.

Response analysis will be performed in accordance with the Response Evaluation Criteria in Solid Tumors (RECIST) version 1.1 [12], for each functional liver lobe separately. Disease control rates (percentage of liver lobes with complete response, partial response or stable disease) will be determined by CT evaluation at 3 months posttreatment. Metabolic tumor response will be determined by assessing the change (relative to baseline) in total lesion glycolysis values on ^18^F-FDG-PET imaging. During the response assessment, observers will be blinded for the catheter type used.

The relationship between tumor absorbed dose on SPECT/CT and tumor response on both CT and ^18^F-FDG-PET will be characterized on the level of perfusion territories.

Common Terminology Criteria for Adverse Events v 4.03 will be used to describe laboratory and clinical toxicity for the entire cohort, with specific attention for device-related adverse events per catheter type such as the occurrence of reflux, vasospasm, or arterial dissections.

The municipal administration will be consulted to assess the overall survival, measured from treatment onward.

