### Statistical considerations

#### Sample size calculation

A subgroup analysis of the T/N activity ratios in seven patients with CRLM, previously treated with ^166^Ho RE using a SMC [3], showed a mean T/N ratio of 1.6 (standard deviation 0.57). Sample size calculation, based on a two-sided paired *t* test for the comparison of T/N activity concentration ratios at an alpha level of 0.05 and power of 0.90, showed that at least 23 patients need to be included to detect a difference of 0.4 in mean T/N ratios (with an estimated standard deviation 0.57) in the ARC arm (estimated mean T/N ratio 2.0) and SMC arm (estimated mean T/N ratio 1.6). This corresponds to a 25 % increase (considered clinically relevant) in favor of the ARC arm. A rounded number of 25 patients will therefore be treated in this trial. Sample size calculations were performed with the computer program ‘PS: Power and Sample Size Calculation’ version 3.0 for MacOsX.

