#### Randomization

A computer-generated stratified permuted block randomization with varying block sizes will be used. Difference in tumor burden (<10 % or ≥ 10 %) between the two target volumes in the liver will be used as stratification factors to eliminate the potential influence of tumor burden on the comparison of T/N activity ratios between catheter types.

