#### Statistical analysis

A comparison of continuous outcome measures between ARC and SMC infusions, such as the mean T/N activity concentration and mean decrease in total lesion glycolysis at 3 months posttreatment, will be performed by means of a paired *t* test. Categorical outcome measures, such as infusion efficiency and disease control rates at 3 months posttreatment, will be compared with a McNemar’s test. The value of the ^166^Ho scout dose distribution will be assessed per catheter type. Correlation and agreement with the ^166^Ho therapy dose distribution will be evaluated with a linear regression analysis (R^2^) and Bland-Altman analysis (limits of agreement), respectively. The dose-response relationship will be evaluated by linear regression analysis. Survival analysis by the Kaplan-Meier method will be used to estimate the median overall survival time for the entire cohort. The primary analyses will be performed on an intention-to-treat (as randomized) basis.

A two-sided *p* value < 0.05 will be considered statistically significant.

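### The dose-response regression should carry baseline tumour burden as a covariate: the activity rule ties tumour dose to burden, so the regression as stated is confounded if burden also affects response

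*Protocol article*

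**What the plan says.** Treatment planning sets the total activity as that "required to deliver a whole liver absorbed dose of 60 Gy", and adds that "The treatment activity for each perfusion territory is fractionated based on its liver volume". Tumour burden does not enter this rule.

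Study objectives lists a dose-response relation between tumour absorbed dose and tumour response among the secondary objectives. Under Outcome assessment, the relation with response on both CT and FDG-PET "will be characterized on the level of perfusion territories". Statistical analysis gives the method in one sentence: "The dose-response relationship will be evaluated by linear regression analysis". No covariate is named, and none is ruled out.

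Burden is handled in one place. Randomization stratifies on the difference in burden between the two target volumes (below 10%, or 10% and above) "to eliminate the potential influence of tumor burden on the comparison of T/N activity ratios between catheter types".

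**The concern.** The catheter comparison is randomised within the patient. The dose-response analysis is not: the tumour dose of a territory results from its anatomy, its T/N and its tumour fraction. The stratification protects the catheter comparison and does nothing for a regression of response on dose.

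With the mean territory dose fixed by volume, tumour fraction helps to determine tumour dose. If tumour fraction also influences response by a route other than dose, it is a common cause of both sides of the regression. A slope could then partly reflect how lightly or heavily involved lobes respond, and a reader could not separate that from an effect of dose. This is a different issue from having two territories per patient, and from the scale on which response is measured.

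**Working it through.** **The plan's own figures.** None is given for the dose-response regression. The only computed design figure is the 23 patients for the paired t test, and it reproduces closely if 0.57 is the SD of the paired differences. The normal formula gives (0.57 × (1.960 + 1.2816) / 0.4)² = 21.3, so 22; the noncentral t gives power 0.895 at 23 and 0.920 at 25. The T/N inputs below come from that section.

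**Inputs from the article.** Mean dose 60 Gy, split by territory volume (Treatment planning). T/N mean 1.6 with SD 0.57 for the standard microcatheter, and mean 2.0 for the anti-reflux catheter (Sample size calculation). 25 patients × 2 territories = 50 units.

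**Step 1: tumour dose against burden.** Let R be T/N, read as a concentration ratio, and f the tumour fraction of the territory. Assume the planned activity is delivered in full. The mean dose is then f·D_T + (1 − f)·D_T/R = 60, which gives

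D_T = 60R / (1 + f(R − 1)).

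| T/N | f = 5% | 20% | 40% | 60% |
|---|---|---|---|---|
| 0.8 | 48.5 | 50.0 | 52.2 | 54.5 |
| 1.0 | 60.0 | 60.0 | 60.0 | 60.0 |
| 1.6 | 93.2 | 85.7 | 77.4 | 70.6 |
| 2.0 | 114.3 | 100.0 | 85.7 | 75.0 |

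(Doses in Gy.) At T/N 1.6 and f = 50% the dose is 96/1.30 = 73.8 Gy, which is 93.2 − 73.8 = 19.4 Gy below the value at 5%. Dose falls with burden above T/N 1, is constant at 1 and rises below 1.

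**Step 2: how far this carries into the regression.** The following are assumptions, because the article gives no burden distribution and no burden-response correlation. The 50 territories are independent; T/N is lognormal with SD 0.57 and independent of burden; f is uniform from 2% to a stated maximum; dose has no true effect; and response worsens with burden, with a correlation of size rho. Each scenario has 4,000 runs. The entries are rejection rates at two-sided 0.05 for response regressed on dose alone.

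| Mean T/N | Burden up to | corr(dose, f) | rho 0 | 0.3 | 0.5 | 0.7 |
|---|---|---|---|---|---|---|
| 1.6 | 20% | −0.12 | 0.05 | 0.06 | 0.07 | 0.10 |
| 1.6 | 40% | −0.24 | 0.05 | 0.08 | 0.14 | 0.22 |
| 1.6 | 60% | −0.36 | 0.05 | 0.12 | 0.25 | 0.44 |
| 2.0 | 20% | −0.21 | 0.05 | 0.08 | 0.12 | 0.18 |
| 2.0 | 40% | −0.43 | 0.05 | 0.15 | 0.33 | 0.59 |
| 2.0 | 60% | −0.59 | 0.05 | 0.24 | 0.58 | 0.89 |

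As a check, the spurious dose-response correlation should be about |corr(dose, f)| × rho. At T/N 1.6, burden up to 60% and rho 0.5 that is 0.362 × 0.5 = 0.181; the simulated value is 0.183.

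**Step 3: with burden in the model.** Adding f as a covariate returns the rejection rate to about 0.05 in every scenario.

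**The case against.** The strongest reply concerns scope. One sentence in a condensed article neither lists nor excludes covariates, and those of a secondary regression are commonly left to the full protocol or the SAP. No passages contradict each other and no figure is wrong. That stands: silence does not show that burden is excluded, and this is not a demonstrated error. What remains is that a specific, better model than the stated one is available at almost no cost.

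Three stronger readings are tempting, and the documents support none of them.

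- *Burden alone can create a dose-response relation.* It cannot. Burden must also affect response independently of dose, which no passage says. Without that link the rate stays at 5%.
- *The slope is biased away from zero.* The direction is not fixed. Metabolic response is a change relative to baseline, and the article does not say how baseline burden relates to relative change. If heavily involved lobes showed larger relative decreases, the bias would reverse and could hide a true dose effect. The dose side can also flip: T/N = 1 lies only (1.6 − 1)/0.57 = 1.05 SD below the planning mean. The Discussion does report T/N of 1 or below, though for individual tumours and not for territories.
- *The distortion is large.* Burden is not the main source of dose variation. At f = 20%, moving T/N from 1.03 to 2.17 (±1 SD) moves tumour dose from 61.4 to 105.5 Gy, about 44 Gy. At T/N 1.6 burden explains 0.115² = 1% to 0.362² = 13% of dose variance over the ranges simulated. The high rates need wide burden ranges and strong links together. The recovery to 5% is also expected, because burden is the only confounder simulated.

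It is also fair that the Discussion rests its expectation of better response on dose-response relations already reported elsewhere. The trial's own randomised evidence on response is the within-patient catheter comparison, which this issue does not touch.

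**Conclusion.** The point holds in conditional form. That tumour dose depends on burden follows from the article's own activity rule whenever territory T/N differs from 1, and at both planning means tumour dose falls as burden rises. Whether this confounds the regression depends on a burden-response link that the article neither states nor excludes, and the sign of that link sets the direction. The size is uncertain: no inflation without a link, 6% to 10% at T/N 1.6 with burden up to 20%, and much more only under wide ranges and strong links. These rates assume a uniform burden distribution, the rho values shown, T/N independent of burden, and independent territories.

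This is a low-cost improvement to a secondary analysis. It does not bear on the primary endpoint, and it is no criticism of the activity rule.

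**What to change.** In Statistical analysis, state that the CT and PET dose-response regressions include the territory's baseline tumour burden (tumour fraction of the target volume) as a covariate, with its scale fixed in advance. Report the adjusted dose slope with its 95% CI beside the unadjusted slope. If the full protocol or SAP already does this, only the article's sentence needs to match.

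Burden is measured before treatment, so it does not lie on the path from dose to response. Conditional on it, the slope reflects dose differences between territories of equal burden, which under the mass balance come from T/N.

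No new data are needed, because assigning the randomisation strata already requires the burden of both target volumes. The cost is one degree of freedom and a somewhat wider interval for the dose slope.

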#### Study organization

Data completeness and accuracy will be frequently checked by the Department of Radiology and Nuclear Medicine, University Medical Center Utrecht. An independent clinical research associate (Julius Clinical, Zeist, The Netherlands) will audit the trial conduct during 3–4 visits. Appointing a data safety monitoring board was not required for this trial. As per Dutch regulations, serious adverse events, serious adverse device effects, and protocol violations are recorded and reported to the institutional review board. There are no stop rules in this study. No interim analysis is planned.

## Discussion

In patients with advanced colorectal cancer, liver metastases are the primary cause of morbidity and mortality. Unfortunately, only a minority of patients is a candidate for surgical resection with curative intent. Patients with irresectable disease will first receive palliative systemic therapy. Though, despite major advances in systemic treatment, overall survival remains disappointing in this subgroup of patients [13, 14].

Current standard of care in the systemic treatment of metastatic colorectal cancer is based on cytotoxic fluoropyrimidines, oxaliplatin, and irinotecan, as well as targeted therapy with the vascular endothelial growth factor (VEGF)-targeted monoclonal antibody bevacizumab [15–19]. There is no clear preference for sequential exposure to these drugs during consecutive lines of treatment or upfront combination therapy [20, 21]. When disease progression or intolerable toxicity occurs during first-line treatment, patients will subsequently receive another regimen as second-line treatment, with the choice of the regimen depending on the first chemotherapeutic agents. In the Netherlands, the first-line regimen of choice is CAPOX-B (capecitabine, oxaliplatin, and bevacizumab). After initial treatment with six cycles of CAPOX-B, maintenance therapy with capecitabine and bevacizumab is given until disease progression [22]. Subsequently an irinotecan-based regimen, e.g., FOLFIRI (leucovorin, fluorouracil (5-FU), and irinotecan) or irinotecan monotherapy, is indicated as second-line therapy. Only patients with a KRAS wild-type tumor may benefit from additional (third-line) treatment with an epidermal growth factor receptor (EGFR)-targeted monoclonal antibody (panitumumab or cetuximab).

Liver-directed therapy such as RE is increasingly applied as an alternative to achieve local disease control. Currently, two types of yttrium-90 microspheres are used in worldwide clinical practice: resin (SIR-Spheres, SIRTeX, Lane Cove, Australia) and glass (TheraSphere; BTG, Ottawa, ON, Canada) yttrium-90 (^90^Y) microspheres. In salvage patients with colorectal liver metastases, who have no regular treatment options left and an average life expectancy of less than 6 months, median overall survival after RE treatment with ^90^Y microspheres is around 12 months when given as monotherapy or in combination with chemotherapy [1]. Besides, treatment is generally well tolerated, with typical clinical toxicity being limited to mild symptoms of fatigue, abdominal pain, nausea, vomiting and/or fever during the first 2 weeks after treatment [23].

Despite these benefits of RE, there is still room for improvement. Unintentional deposition of radioactive microspheres in tissues other than the liver may cause serious treatment complications. Therefore, a safety procedure is performed in the week(s) before the actual treatment. During this procedure, coil embolization of extrahepatic branches may be performed and a strategic catheter position is chosen before administering a (harmless) scout dose of technetium-99 m-labelled macro-aggregated albumin (^99m^Tc-MAA). Afterward, SPECT/CT and planar nuclear scintigraphy are obtained to exclude the presence of extrahepatic activity and significant liver-to-lung shunting. The treatment procedure is typically performed 1–2 weeks later, with the administration of ^90^Y microspheres from identical catheter positions, followed by posttreatment imaging with bremsstrahlung SPECT/CT or ^90^Y-PET/CT [24].

As a second topic of possible improvement, the intrahepatic distribution of therapeutic ^90^Y microspheres cannot be accurately predicted in advance. The scout dose of ^99m^Tc-MAA particles differs markedly in embolic effect, size, weight, and number of particles infused [25], and therefore fails to predict the intrahepatic distribution of ^90^Y microspheres in most cases [26–28]. Besides, imaging of the ^90^Y microspheres biodistribution itself is already a challenge due to the lack of γ-radiation emission. Traditionally, bremsstrahlung SPECT/CT has been used for posttreatment imaging, but it suffers from a low spatial resolution. Internal-pair production-based ^90^Y-PET/CT has become available as an alternative for quantitative imaging, but the low count rate and inherent noise limit its applicability in daily clinical care [29–31].

Third, it is generally assumed that the preferential arterial vascularization of liver tumors will lead to a selective targeting of tumorous tissue following intra-arterial infusion of radioactive microspheres. It is known from pathological examinations of livers treated with ^90^Y RE that radioactive microspheres cluster preferentially within the peripheral tumor vasculature. The concentration of microspheres can be up to 200 times greater in the tumor periphery than in the tumor center and the healthy liver tissue [32]. Various studies have investigated dose-response relationships in RE. The majority of these studies found strong associations between T/N ratios, absorbed radiation doses, tumor response and overall survival [27, 33–39]. Yet, the degree of tumor targeting, as expressed by the T/N microsphere uptake ratio, shows marked interindividual variability in practice, with a reported range of 0.6–25.9 [40]. This heterogeneity in T/N uptake ratios is likely a result of various factors, including differences in tumor angiogenesis, microsphere characteristics, catheter position, and flow-bound distribution physics [25, 33]. A recent investigation demonstrated that up to 60 % of patients with liver metastases treated with ^166^Ho RE had at least one tumor that received less than or an equal amount of radioactivity as compared to the surrounding healthy liver tissue (T/N ≤ 1) [4]. Flamen et al., also reported similar findings, with 38 % of the metastatic liver lesions in their study having an unfavorable T/N uptake ratio (<1) after RE with ^90^Y microspheres [39]. Since unfavorable T/N uptake ratios cannot be predicted and only become apparent after treatment, timely adjustments in treatment technique are not yet feasible.

The highly variable tumor targeting is an important clinical problem that may at least explain some of the inconsistencies in reported tumor response rates after RE [1, 41]. Considering the reported dose-response relationship, it can be expected that improved T/N ratios will positively affect tumor response after RE. It may also reduce hepatotoxicity, since healthy liver tissue absorbed dose has previously been correlated to biochemical toxicity [37]. Improvement of T/N ratios is especially important in CRLM, since metastases from this tumor type are relatively hypovascular compared with other tumor types (such as neuroendocrine tumors or uvea melanoma), and generally exhibit low T/N ratios.

The above outlined shortcomings of current RE practice are being addressed in the SIM trial, for which trial accrual has started as of November 2014. The distinctive imaging capacities and availability of an identical scout dose of ^166^Ho microspheres, combined with the promising effects on particle fluid dynamics facilitated by the ARC, may result in an optimized treatment technique of RE in patients with CRLM.

### Trial status

Patient recruitment was ongoing at the time of submission.
